To take into consideration all these aspects, an interesting approach is to regard the patient with a whole system approach, as presented in the biopsychosocial or social-ecological model [11]. Based on this approach, the Social-Ecological Model of Adolescent and Young Adult Readiness to Transition (SMART) proposes a conceptual framework that describes factors influencing paediatric-adult transition in SCD [12]. This includes bioclinical factors such as complications, psychological factors such as pain perception, and social factors such as scholar absenteeism [12]. Some of these factors may be modified and therefore these could become part of the patient’s coping skills [11, 12]. For instance, a coping skill for managing complications may be knowing when to go to the hospital based on a patient’s own pain threshold. For this, a pluridisciplinary team is required [12].

Currently, only pilot studies of transition programmes based on biopsychosocial approaches have been performed [13–16], with encouraging primary results [13].

The DREPADO open-label, individual, multicentre, randomised controlled trial (RCT) proposes to assess a paediatric-adult transition program for patients with SCD based on a biopsychosocial approach and SMART compared to standard care management. As compared to available studies that have investigated the paediatric-adult care transition [13], the originality of this study is the biopsychosocial approach coupled to its randomised controlled design. The purpose of the article is to present the DREPADO study protocol.

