### Sample size and recruitment

A total of 196 (98 in each group) is required to detect at least a 15% reduction of the hospitalisation rate for complications 2 years after the transfer in the intervention group compared to the control group. This reduction assumes a hospitalisation rate of 3.5 per patient per year [7] with 80% power and the use of a two-sided test at a significance level of 5% and a 10% inflation factor to anticipate study deviations (missing data, withdrawal, loss to follow-up).

Participants are recruited in the hospital when they come for a medical consultation or at the end of a hospitalisation for complications. Potential participants are screened. The investigator informs the patient and caregiver about the study, following which the patient gives oral consent and the patient’s caregiver the written informed consent for patient participation. The information note and consent form is presented in Additional file 1. When the patient legally becomes an adult (i.e. at 18 years of age in France), he will give his/her own written informed consent.

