#### Arm B – intervention group

In addition to standard management, patients and caregivers randomised to the intervention group benefit from the SCD paediatric-adult transition programme. Based on the biopsychosocial approach, this consists of three structured axes, the objectives of which and practical details are summarised in Table 1.

**Table 1 Tab1:** The three axes of paediatric-adult transition programme

Axes	Public	Objectives	Contents	Practical details	Providers
Educative	Patient and caregiver dyad	Providing self-care knowledge and skills related to SCD and therapeutics	Knowledge and coping skills, with patient needs assessment	Face to face At patients’ home 3 sessions of 2 h	One healthcare professional, trained in patient education and in SCD
Psychological	Individual patient i	Helping empower patients in relation to pain management and emotions	Knowledge and coping skills, with patient needs assessment	Face to face At hospital 6 sessions of 1.5 h	One healthcare professional, trained in therapeutic hypnosis and in SCD
Social	Group of 4 to 8 patients	Facilitating the relationship with oneself, others, and care	Coping skills	Face toface At ‘neutral place’ as association patient place 2 sessions of 2 h	One healthcare professional and one expert patient, both trained in patient education and in SCD

*h* hour*, SCD* sickle cell disease

The modifiable factors are used as coping skills during the educative, the psychological, and the social axis. The objective of the educative axis is to provide knowledge and coping skills related to self-care management. It is conducted at home with the patient and his/her parent by a healthcare professional trained in patient education. The objective of the psychological axis is to help empower patients in relation to pain management and emotions. It is conducted at hospital with only the patient by a healthcare professional trained in therapeutic hypnosis. The objective of the social axis is to facilitate the relationship to oneself, others, and care. It is conducted in a ‘neutral place’ (not at home and not at the hospital) with a group of patients by a healthcare professional trained in patient education and an expert adult patient also trained in patient education.

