### Outcome measurements

The primary outcome is number of hospital admissions and emergencies in the index hospital for complications (i.e*.* VOC, ACS, and/or stroke) in the 2 years after T-transfer.

To evaluate the biopsychosocial approach, the secondary outcomes include bioclinical, psychological, and social factors, measured at T-inclusion, T-transfer, T-12, and/or T-24, collected from patients and/or parents. With regard to the indirect bioclinical factors, the use of care is evaluated by the incidence of emergency visits and medical consultations at T-24. Medication adherence is also measured at T-inclusion, T-transfer date, T-12, and T-24 by adapted Medication Intake Survey-Asthma (MIS-A) [17] adapted for SCD and Medication Adherence Report Scale (MARS) [18]. Psychological factors, such as pain perception, and social factors, such as school absenteeism is measured by self-declaration. Quality of life is evaluated using the brief World Health Organisation Quality of Life questionnaire (WHOQOL-Brief), and skills are measured by questionnaires, such as the health literacy using the European Health Literacy Questionnaire (HLS-EU-Q16) [19], self-efficacy feeling using the Self Efficacy Specific Instrument – Sickle Cell Disease (SCD-SES) [20]; these are measured at the T-inclusion, T-transfer, T-12, and T-24. All the data sources are presented in Table 2.

**Table 2 Tab2:** Data collection plan

Outcomes		Time point				Population		Data sources
		T-inclusion	T-transfer	T-12	T-24	Patient	Parent	
Use of care	Hospitalisations for VOC, ACS, stroke		X		X	X		Medical records
	Emergency visits, medical consultations, imaging exams		X		X	X		Medical records
Medication adherence		X	X	X	X	X		2 questionnaires (MARS and adapted-MIS-A)
School absenteeism			X		X	X	X	Auto declaration
Quality of life		X	X		X	X		26-item questionnaire (WHOQOL-Brief)
Health literacy		X	X		X	X		16-item questionnaire (HLS-EU-Q16)
Disease and therapeutic knowledge		X	X		X	X	X	36-item questionnaire
Patient activation		X	X		X	X		13-item questionnaire
Sense of self-efficacy						X		9-item questionnaire (SCD-SES)
Transition preparation		X	X		X	X		20-item questionnaire (TRAQ)
Pain perceptions	At home			X	X	X		Auto declaration (book)
	Intensity during hospitalisations		X		X	X		Medical records

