### Statistical analysis plan

Demographics and other characteristics are reported descriptively and according to treatment group. Means and standard deviation (SD), or medians and ranges when appropriate are calculated for continuous variables. Categorical variables will be presented using numbers and percentages.

The crude rate of hospitalisations due to complications will be calculated by dividing the total number of hospitalisations due to VOC, ACS, and stroke occurring after transfer by the total duration of follow-up of all patients in each group. The treatment effect will be assessed using a multivariable Poisson regression model with the study group as a factor, adjusting for minimisation factors and relevant patient characteristics and the length of follow-up as the offset. Results will be expressed as a rate ratio with 95% confidence interval. A negative binomial model will be fitted if data are over-dispersed. The same analyses will be performed for the association between intervention and other secondary outcomes.

Analysis of covariance (ANCOVA) will be used to evaluate the intervention effect at T-24 on all the secondary outcomes evaluated by questionnaires. Scores will be computed and depicted at each assessment by following the scoring procedures for each questionnaire. Each ANCOVA will include the baseline measure (T-inclusion) and minimisation factors as covariates. Changes over time for each score will be also assessed using generalized estimation equation analyses to test the effect of group, time, and the interaction group time after controlling for minimisation factors and relevant patient characteristics.

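### Pain intensity during hospitalisations is observed only in admitted episodes, which the programme aims to reduce, so a between-arm test of it is open to selection bias of unknown direction and size

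*Protocol article*

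**What the plan says.** Under Outcome measurements, Table 2 of the protocol article splits pain perceptions into two rows. Pain at home comes from a patient book at T-12 and T-24. The other row, "Intensity during hospitalisations", comes from medical records at T-transfer and T-24, with no T-inclusion value. (The text of that section says "Psychological factors, such as pain perception, and social factors, such as school absenteeism is measured by self-declaration", which fits the first row but not the second.)

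The primary outcome is the "number of hospital admissions and emergencies in the index hospital for complications", counted over the two years after transfer.

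The Statistical analysis plan section describes a Poisson or negative binomial rate model for the primary outcome and then states: "The same analyses will be performed for the association between intervention and other secondary outcomes". ANCOVA is kept for outcomes evaluated by questionnaire. The article says nothing specific about in-hospital pain.

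On the programme itself, the Background gives "knowing when to go to the hospital based on a patient’s own pain threshold" as an example of a coping skill, and the Arm B section says: "The modifiable factors are used as coping skills during the educative, the psychological, and the social axis".

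**The concern.** An in-hospital pain score exists only when a crisis leads to admission. Admission happens after randomisation and is part of what the programme is designed to reduce. Comparing the scores by arm therefore compares two sets of episodes that the programme itself may have shaped. The T-transfer value also falls after randomisation, and with no T-inclusion value there is no baseline for adjustment.

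Selection by pain is plausible here, because the Background links going to hospital with the patient's own pain threshold. If milder crises were kept out of hospital in Arm B, the remaining admissions would look more painful although no crisis had become worse. If severe crises were the ones prevented, Arm B would look better for an equally uninformative reason. The intensity data alone cannot show which has happened, so a significant difference could be reported as harm or as benefit without support.

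**Working it through.** **Inputs from the protocol article (Sample size and recruitment).** The calculation "assumes a hospitalisation rate of 3.5 per patient per year", which is 7.0 over two years in Arm A. The target is a 15% reduction, so 7.0 × 0.85 = 5.95 in Arm B. Power is 80%, the two-sided level 5%, inflation 10%, and 98 patients are planned per arm.

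**The plan's own figure.** On the log rate-ratio scale, with the null variance in the significance term and the alternative variance in the power term:

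n = [1.960·√(2/7) + 0.842·√(1/7 + 1/5.95)]² / (ln 0.85)² = (1.048 + 0.469)² / 0.0264 = 87.1, so 88.

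88 / 0.90 = 97.8, so 98 per arm and 196 in total. This matches the plan, so these rates can be used below.

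**How many patients have no value?** P(no admission in two years):
- Poisson: e^(−7) = 0.09% in Arm A; e^(−5.95) = 0.26% in Arm B.
- Negative binomial, shape 1: 1/8 = 12.5%; 1/6.95 = 14.4%.
- Negative binomial, shape 0.5: √(0.5/7.5) = 25.8%; √(0.5/6.45) = 27.8%.

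The arms differ by at most about 2 percentage points. Which patients have a value changes little; what can change is which episodes are observed.

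**Size of the artefact with no true effect on intensity.** Assumptions not in the documents: intensity is normal with SD 1 across crises, half of its variance lies between patients, and counts are Poisson or negative binomial with shape 1.

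Shift per episode:
- 75% of prevented admissions from the milder half: the half-normal mean is 0.798, so prevented episodes average −0.75·0.798 + 0.25·0.798 = −0.399, and the shift is 0.15·0.399/0.85 = +0.07 SD.
- Exactly the mildest 15% prevented: φ(z₀.₁₅)/0.85 = 0.233/0.85 = +0.27 SD.

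Shift in per-patient means, and rejection rate of a nominal 5% test, from a simulation with 88 evaluable patients per arm and 1,000 runs (Poisson / shape 1):

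| Admissions prevented in Arm B | Shift, SD | Rejection |
|---|---|---|
| None | −0.002 / 0.003 | 5.9% / 5.1% |
| 15%, unrelated to intensity | −0.005 / 0.008 | 5.7% / 5.8% |
| 15%, three quarters from the milder half | 0.037 / 0.037 | 6.2% / 6.5% |
| Exactly the mildest 15% | 0.199 / 0.200 | 50.2% / 39.4% |
| Exactly the most severe 15% | −0.196 / −0.211 | 49.8% / 44.4% |

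**A sharp-threshold variant.** Suppose only a fraction p of crises is attended in Arm A, 0.85p in Arm B, and every attended crisis is worse than every crisis kept at home. Mean intensity among attended crises is φ(c)/p, with c the threshold. For 80% against 68% the shift is 0.526 − 0.350 = 0.176 SD per episode. For p from 60% to 95% it runs from 0.138 to 0.230 SD. These figures depend on the perfectly sharp threshold and belong with the extreme rows of the table.

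**The case against.** The strongest reply is that Table 2 is a data collection plan and nowhere describes a test of this row. A rate model with a follow-up offset does not suit an intensity score, and a condensed article may leave the detail to a statistical analysis plan that is not shown. This stands in part: how the scores would be summarised is open. But the general sentence, read literally, covers every secondary outcome outside the questionnaires, so the article does state a rule, and that rule is unsuited to this row.

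A reader might also infer more than the documents support:
- **That the comparison is certainly biased, and against Arm B.** Bias needs the prevented admissions to differ in intensity from those that remain, and nothing in the documents establishes that or its direction. Under partial selection the rejection rate is barely above nominal.
- **That many patients lack a value.** On the plan's own rate almost none do. Even with strong over-dispersion the arms are nearly equal in this respect.
- **That the programme teaches attendance thresholds.** The Background offers this only as something a coping skill may be. Neither Table 1 nor the Arm B section lists it as content.

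**Conclusion.** The point holds as a risk to interpretation. A between-arm comparison of in-hospital pain intensity conditions on an event the programme is meant to change, so it is open to selection bias of unknown direction and size. With 15% of admissions prevented, the artefact ranges from about zero, through about 0.04 SD per patient under partial selection, to about 0.2 SD per patient in either direction at the extreme. The sizes rest on the distributional assumptions stated with the calculation. The rates are the protocol's own. One secondary outcome is affected; the primary analysis and the sample size are not.

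**What to change.** In the Statistical analysis plan section, exempt pain intensity during hospitalisations from the sentence that extends the primary analysis to other secondary outcomes. State that it will be reported descriptively by arm, next to the number of admissions, with no claim of a treatment effect on pain.

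Home pain from the book at T-12 and T-24 does not require an admission and can carry the pain comparison. Its caveats should be written down: it is self-report in an open-label trial, it has no baseline, and it may itself rise in Arm B if milder crises are managed at home. A summary defined for everyone, such as days in hospital with severe pain, should not be promised unless daily in-hospital pain is recorded; Table 2 does not list it.

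The cost is a change of wording and one fewer inferential secondary comparison. No new data are needed.

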### Data collection and management

#### The data collection plan is presented in Table 2

The study data will be collected on a secure electronic case report form (eCRF) (Ennov Clinical, version 7.5.710.4, San Francisco, CA, USA), that will be available at each centre through an Internet portal. In each centre, eCRF users have their own personal login. A clinical research associate, delegated by the centre investigator and who is trained in GCP, enters data into the eCRF.

No personal identifying information will be mentioned on the eCRF. Each patient included the study will be assigned a unique identification number that will consist of the identification number of the investigational centre, the initials of the patient, and the chronological inclusion number of the patient.

Multiple external validation checks will be applied: examination of the source documents and cross-checking with the data recorded in the eCRF as to its accuracy, the presence of missing data, and the consistency of data. The eCRF will only include the data necessary for the analysis to be reported in a scientific publication.

All study data will be stored securely at Lyon University Hospital. All electronic data will be secured on a password-protected laptop. Paper-based study documents will be stored in a secure filing cabinet at each centre. All electronic documents containing names or personal identifying information, necessary for the follow-up of the study, will be stored separately from other study data and protected by a code number. Access to these files will be limited to research staff involved in the study.

The trial statisticians will have access to the data set for the final analysis of trial outcomes. They will receive checked and validated data from the eCRF with no personal identifying information.

### Monitoring and participant safety

The Trial Steering Committee (TSC) will be responsible for overseeing the progress of the trial and will meet at regular intervals. The TSC includes the principal investigator, the investigators of the centres, and the trial coordinators/project managers. The TSC has developed the study protocol and is responsible for data collection, management, publications, and the final data set. The committee is responsible for finding solutions to unforeseen questions/problems that may arise in the course of the study.

One monitoring session will be conducted per year in each centre by the clinical research department of the Lyon University Hospital. To ensure conformity to GCP, the medical records, informed consent forms, and the eCRFs will be checked.

No interim analysis or harms are expected, and therefore no premature stop of the trial is anticipated and no auditing by an independent committee is needed. According to French law, the study does not require a formal data monitoring committee as it is a trial with known minimal risks.

### Statistical analysis plan

Demographics and other characteristics are reported descriptively and according to treatment group. Means and standard deviation (SD), or medians and ranges when appropriate are calculated for continuous variables. Categorical variables will be presented using numbers and percentages.

The crude rate of hospitalisations due to complications will be calculated by dividing the total number of hospitalisations due to VOC, ACS, and stroke occurring after transfer by the total duration of follow-up of all patients in each group. The treatment effect will be assessed using a multivariable Poisson regression model with the study group as a factor, adjusting for minimisation factors and relevant patient characteristics and the length of follow-up as the offset. Results will be expressed as a rate ratio with 95% confidence interval. A negative binomial model will be fitted if data are over-dispersed. The same analyses will be performed for the association between intervention and other secondary outcomes.

Analysis of covariance (ANCOVA) will be used to evaluate the intervention effect at T-24 on all the secondary outcomes evaluated by questionnaires. Scores will be computed and depicted at each assessment by following the scoring procedures for each questionnaire. Each ANCOVA will include the baseline measure (T-inclusion) and minimisation factors as covariates. Changes over time for each score will be also assessed using generalized estimation equation analyses to test the effect of group, time, and the interaction group time after controlling for minimisation factors and relevant patient characteristics.

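### The count model with a follow-up offset is extended to other secondary outcomes without limit, and it does not suit pain intensity during hospitalisations

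*Protocol article*

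**What the plan says.** The Statistical analysis plan section opens its inferential part with hospitalisations for complications, which are compared between arms by Poisson regression. On covariates and exposure time it specifies: "adjusting for minimisation factors and relevant patient characteristics and the length of follow-up as the offset". The effect measure is a rate ratio with its 95% confidence interval. The only alternative within this route is "A negative binomial model will be fitted if data are over-dispersed". The paragraph ends by extending the approach: "The same analyses will be performed for the association between intervention and other secondary outcomes".

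The next paragraph gives the second route. Outcomes measured by questionnaire are compared at T-24 by ANCOVA with the T-inclusion value and the minimisation factors as covariates, and their scores over time by generalised estimating equations. No third model is named.

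Table 2 (Outcome measurements) has two pain rows. One is "Intensity during hospitalisations", from medical records, at T-transfer and T-24. The other is pain at home, self-declared in a book, at T-12 and T-24. Neither is listed as a questionnaire.

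**The concern.** With two routes, and the second reserved for questionnaires, pain intensity in hospital falls to the first. That model estimates events per unit of time. A pain intensity is a level on a scale. It is not a number of events, and it does not grow because the patient is observed for longer. Dividing it by follow-up gives a quantity with no clinical meaning, and the comparison between arms then depends on how long each arm was followed.

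Unequal follow-up is possible here. Under Withdrawal and discontinuation, absence from the intervention as well as from evaluation can lead to a participant being classed as a dropout after four unsuccessful calls. Only Arm B has programme sessions to miss (3 + 6 + 2 = 11 in Table 1). The Discussion names adherence to the programme as a potential limitation.

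Pain management is also the stated aim of the psychological axis, so this is one of the secondary results that readers will look at.

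**Working it through.** **The plan's own figure.** The only computed design figure is the sample size, and this point does not dispute it. With 3.5 admissions per year over 2 years, the expected counts are 7 in Arm A and 7 × 0.85 = 5.95 in Arm B. A Poisson formula with the null variance at the control rate gives, per arm,

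[1.960 × √(2/7) + 0.842 × √(1/7 + 1/5.95)]² / (ln 0.85)² = 87.1, so 88.

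Then 88/0.90 = 97.8, so 98 per arm and 196 in total, as stated.

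**Scale.** With the log of follow-up as offset, the model describes score divided by years. A score of 6 out of 10 becomes 6/1 = 6.0 per year after one year and 6/2 = 3.0 per year after two. The pain is the same, but the value is halved.

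**Equal follow-up in both arms.** The follow-up times cancel and the ratio is unbiased. The variance is still wrong. For a mean score m with standard deviation s, Poisson takes the variance as m, while the true variance is s². The standard error is therefore too large by the factor √(m/s²). The documents give neither value, so these are assumptions:

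- m = 5, s = 2: √(5/4) = 1.12, so intervals are 12% too wide.
- m = 6, s = 2: √(6/4) = 1.22, so intervals are 22% too wide.

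A simulation with m = 6, s = 2, 98 per arm, no dropout and no true effect rejected in 1.5% of 1,500 runs instead of 5%. Such a score is under-dispersed, so the switch to a negative binomial model would not be triggered and would not help.

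**Unequal follow-up.** With equal mean scores, the fitted ratio (B to A) is mean follow-up in A divided by mean follow-up in B. Assume completers are followed for 2 years and dropouts for a time uniform on 0.5 to 2 years (mean 1.25). Mean follow-up is then 2 − 0.75d for dropout proportion d. Rejection rates are from simulation with no true effect (88 per arm, m = 5, s = 2).

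| Dropout A / B | Mean follow-up A / B (years) | Null ratio | Rejection at 5% |
|---|---|---|---|
| equal | equal | 1.00 | about 4% |
| 8% / 12% | 1.940 / 1.910 | 1.02 | 4.3% |
| 5% / 15% | 1.9625 / 1.8875 | 1.04 | 7.5% |
| 10% / 30% | 1.925 / 1.775 | 1.08 | 22% |

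The second and third data rows average 10% dropout, the allowance under Sample size and recruitment. The last row exceeds it.

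If dropouts leave earlier (uniform on 0.25 to 2 years, mean 1.125) and m = 6 with 98 per arm, 5% against 15% gives (2 − 0.875 × 0.05)/(2 − 0.875 × 0.15) = 1.956/1.869 = 1.05, with 9.5% rejection. In the same setting without the offset the ratio is 1.00 and rejection 1.4%.

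**The case against.** The strongest reply is that this is loose wording in a condensed article. The sentence closes a paragraph about hospitalisation counts. Its natural referents are the other use-of-care counts (emergency visits, consultations, imaging exams), for which the model is right. A reader might infer that every secondary outcome outside the questionnaires is sent to the count model. The documents do not support that: the sentence does not say so, and nothing suggests that cost-effectiveness, implementation or lived experience are meant to be analysed this way. This part of the reply stands. It does not rescue pain intensity, which is a tabulated patient-level outcome for which no other model is named.

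A reader might also infer that blank days in the home pain book are counted as pain-free. The article does not say whether the book records days, episodes or scores, how often it is filled in, or how blanks are treated. That detail may stand in the full protocol, which is not shown, so no such error can be attributed to the plan.

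Third, a high false-positive rate needs a dropout gap well beyond what is planned. The 22% above needs a gap of 20 percentage points and an average of 20%, against a planned allowance of 10% for all deviations. Within that allowance the distortion is small.

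Finally, the primary outcome, its model and the sample size are untouched, and the simulations are simplified: they give every patient a score, whereas intensity in hospital exists only for patients who are admitted.

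**Conclusion.** The stated analysis is wrong for pain intensity during hospitalisations. The importance is minor to moderate and limited to secondary outcomes. Two parts do not depend on dropout: the per-year value has no meaning, and the Poisson variance does not fit a bounded score, so a real difference is harder to detect. The second part rests on an assumed mean of 5 to 6 and SD of 2.

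Bias in the ratio between arms arises only if follow-up differs by arm. It is about 2% to 4% at dropout averaging the planned 10% (about 5% if dropouts leave earlier), and about 8% at an assumed 10% against 30%. More loss in Arm B makes the intervention look worse on pain; more loss in Arm A makes it look better.

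For home pain, the documents support only the remark that the right model depends on what the book records.

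**What to change.** - Limit the sentence to outcomes that are event or day counts: emergency visits, medical consultations, imaging exams and, if recorded as days, school absence.
- Name a linear or ordinal model for pain intensity during hospitalisations, adjusted for the minimisation factors and without a follow-up offset. The ANCOVA wording cannot simply be reused, because Table 2 shows no T-inclusion measurement of this outcome.
- State that this outcome is observed only in hospitalised patients. Admission is itself what the programme aims to reduce, so the patients compared are a subset formed after randomisation, and the result should be read accordingly.
- State what the home pain book yields. If it is a score, use the same continuous or ordinal approach. If it is a count of days or episodes, use the number of recorded days as the offset in place of length of follow-up.

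The cost is a few sentences in the analysis section and, if the book yields counts, one derived variable for recorded days. No new data are needed, and the sample size stays at 196.

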## Methods/Design

### The aim, design, and setting of the study

The DREPADO RCT seeks to assess the impact of a paediatric-adult transition programme. This trial is an interventional study. It is an open-label, individual, multicentre RCT comparing a control group (Arm A) to an interventional group with a paediatric-adult transition SCD programme based on the biopsychosocial approach (Arm B).

The DREPADO trial is a French national RCT including centres specialised in SCD patient care, involved in the SCD health network (*Maladie Chronique du Globule Rouge et des autres maladies de l’érythropoïèse* Filière - MCGRE) accredited by the French Ministry of Health and motivated to participate in this study. The coordinating centre is Lyon University Hospital, and five other centres will participate (Créteil, APHP Kremlin-Bicêtre, Martinique, APHP Necker, Pontoise).

The follow-up period is a maximum of 4 years for each patient. Outcomes is assessed at baseline (T-inclusion), at transfer date – which corresponds to the first consultation in the adult department of care (T-transfer), 12 months after transfer (T-12), and 24 months after transfer (T-24).

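### The longitudinal GEE of the questionnaire scores does not condition on the T-inclusion score, so its group term is not a programme effect and its interaction test is less precise than it could be (minor, secondary outcomes only)

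*Protocol article*

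**What the plan says.** The Statistical analysis plan section of the protocol article gives the questionnaire scores two analyses.

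- The first is the designated test of the programme: "Analysis of covariance (ANCOVA) will be used to evaluate the intervention effect at T-24 on all the secondary outcomes evaluated by questionnaires". Its covariates are listed: "Each ANCOVA will include the baseline measure (T-inclusion) and minimisation factors as covariates".
- The second is supplementary and concerns change over time in each score. It is specified as "generalized estimation equation analyses to test the effect of group, time, and the interaction group time after controlling for minimisation factors and relevant patient characteristics". The T-inclusion score is not named in this adjustment set.

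The section on aim, design and setting identifies T-inclusion as the pre-programme visit: "Outcomes is assessed at baseline (T-inclusion), at transfer date". On the number of visits, the Outcome measurements text says of quality of life, health literacy and self-efficacy that "these are measured at the T-inclusion, T-transfer, T-12, and T-24". Table 2 marks no T-12 visit for quality of life or health literacy and no visit at all for self-efficacy; it marks four visits for medication adherence and three for most other scores.

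**The concern.** Two neighbouring sentences treat the baseline score differently. The ANCOVA conditions on it. The GEE is described as an analysis of change and does not list it as a covariate, so it is most naturally read as having T-inclusion among its responses.

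On that reading the group term does not address the programme. Before the programme starts the arms can differ only by chance, and the group term is either exactly that difference or an average that includes it. The interaction does address the programme, but it treats the observed baseline difference as something to be estimated when randomisation already says it is zero, and it spreads the test over several degrees of freedom.

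At stake is how clearly and precisely the longitudinal results are reported for the scores meant to evaluate the biopsychosocial approach, such as quality of life, health literacy, knowledge, patient activation, transition preparation and adherence.

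**Working it through.** **Inputs.** The protocol gives no effect size, SD or correlation for any score, so there is no stated figure for these analyses to reproduce. From the Sample size section: 98 per arm with 10% allowed for deviations, so 98 × 0.9 = 88.2, taken as 88 evaluable per arm. The primary-outcome figure itself reproduces with a Poisson-regression formula at 3.5 × 2 = 7.0 events per patient: [1.96·√4 + 0.8416·√(2 + 2/0.85)]² / (7.0·ln(0.85)²) / 2 = 87.1, rounded up to 88; 88/0.9 = 97.8, i.e. 98 per arm and 196 in total.

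Assumed: unit SD, exchangeable correlation ρ = 0.5, three visits, and an effect d = 0 at T-inclusion and 0.4 SD at each later visit. Power is Φ(d_term/SE − 1.96); the opposite tail is negligible except where the expected value is zero.

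**Step 1. Group term, T-inclusion as reference visit.** It estimates the arm difference at T-inclusion, expected value 0. The rejection rate is 5% whatever the programme does.

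**Step 2. Group term averaged over all visits.** With k visits the expected value is d(k − 1)/k: 2/3 of d for three visits, 3/4 for four. For k = 3: 0.4 × 2/3 = 0.267; SE = √[(2/88)(1 + 2ρ)/3] = √[(2/88)(0.667)] = 0.123; z = 2.17; power 58%.

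**Step 3. Group-by-time, 2 df.** Both changes from T-inclusion have mean 0.4. Their covariance is (2/88) × [[1, 0.5], [0.5, 1]], so the noncentrality is 0.4² × (88/2) × 1.333 = 9.39; power 79%.

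**Step 4. Planned T-24 ANCOVA.** SE = √[(2/88)(1 − ρ²)] = 0.131; z = 3.06; power 86%.

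**Step 5. Baseline-adjusted average over the two post-inclusion visits.** The average has variance (1 + ρ)/2 = 0.75; conditioning on baseline removes ρ² = 0.25 and leaves 0.50. SE = √[(2/88)(0.50)] = 0.107; z = 3.75; power 96%.

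**Step 6. Where the gap between steps 3 and 5 comes from.** A single contrast, the post-inclusion average minus T-inclusion, has variance 0.75 + 1 − 2(0.5) = 0.75, SE 0.131 and power 86%. So roughly 8 points of the gap come from the omnibus test and 10 from not conditioning on baseline.

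**Step 7. The other reading.** If T-inclusion is already a covariate, the group term carries the effect. The interaction then compares only the post-inclusion visits, and for a sustained effect it has expected value 0 and rejects at about 5%.

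**Sensitivity at d = 0.4, three visits** (same formulas):

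| ρ | averaged group term | group-by-time | T-24 ANCOVA | adjusted average |
|---|---|---|---|---|
| 0.3 | 68% | 64% | 79% | 94% |
| 0.5 | 58% | 79% | 86% | 96% |
| 0.7 | 51% | 95% | 96% | 99% |

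With four visits and ρ = 0.5 the averaged group term has 71% and the adjusted average 98%.

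**Simulation checks.** 4,000 simulated trials at d = 0.4 and ρ = 0.5 gave, in the order of steps 1 to 5, 5%, 56%, 80%, 86% and 96%, and 6% for the interaction in step 7. All tests stayed near 5% when there was no effect. Direct GEE fits (500 trials, d = 0.425) gave 5.8% for the reference-coded group term, 63% for the group term in a model without interaction and 83% for the interaction, against 5%, 63% and 84% from the formulas.

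**The case against.** The strongest reply is that the programme effect on the questionnaires is tested elsewhere, and correctly. The T-24 ANCOVA is named for that purpose and conditions on T-inclusion; the GEE is an addition to it. The GEE sentence also contains the term suited to an analysis of change, group-by-time. Nothing says that the group term is to be read as the programme effect. The role of T-inclusion in the GEE is inferred, and coding of terms is detail that a full analysis plan, not shown here, may settle. All of this stands, and it limits the point.

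A reader might go further and infer that a real effect will be reported as absent. The documents do not support that: it would require taking the group term alone and setting aside both the ANCOVA and the interaction. Nor would a null group term contradict a positive ANCOVA, because the two estimate different quantities. The full gap between the group term and the best alternative should not be quoted as the plan's loss of power either, since the plan does not designate that term. The averaged term is not even always the weaker one: with four visits, ρ = 0.3 and d = 0.425 it has 87% against 84% for the ANCOVA.

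What remains is that the protocol itself names a test of group and an adjustment set, and as written that set leaves out a baseline score the trial already collects.

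**Conclusion.** The point holds as a minor improvement to a supplementary analysis of secondary outcomes. If T-inclusion is a GEE response, which is the most likely reading but is not stated, the group main effect cannot answer the programme question. The interaction can, with about 80% power where a baseline-adjusted average would have about 96%. Those two figures rest on 88 evaluable per arm, ρ = 0.5 and a sustained 0.4 SD effect, all assumed; for ρ from 0.3 to 0.7 the difference runs from about 31 points down to about 4. Part of it reflects the omnibus form of the test rather than the handling of baseline. The averaged effect and its dilution also depend on whether a score has three or four visits, on which the outcome text and Table 2 disagree.

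The primary analysis, the sample size of 196, the T-24 ANCOVA and the type I error are unaffected.

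**What to change.** Reword the GEE sentence along these lines: the longitudinal analysis of each score takes the post-inclusion visits as outcomes, with the T-inclusion score and the minimisation factors as covariates; the programme effect is reported as the between-arm difference at each post-inclusion visit and averaged over those visits; group-by-time among the post-inclusion visits serves only to describe whether the effect changes. An equivalent option keeps T-inclusion as a response with the arm means constrained to be equal there. In either case, state that an unadjusted group main effect is not interpreted as the programme effect, and settle which visits apply to each score.

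The cost is wording only, with no new data or patients. The small downside is that patients without a T-inclusion score need the constrained-baseline version or a simple baseline imputation.
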